## Abstract

*Taenia solium* diagnosis is challenging as trained personnel, good diagnostic tools, and infrastructure is lacking in resource-poor areas. This paper aims to describe the study trial design adopted to evaluate a newly developed rapid point-of-care test that simultaneously detects taeniosis and neurocysticercosis (TS POC) in three district hospitals in Tanzania. The two-stage design included three types of patients: patients with specific neurological signs and symptoms (group 1); patients with complaints compatible with intestinal worm infections (group 2); patients with other symptom(s) (group 3). For group 1, all patients were tested using the TS POC test (stage 1), after which all positive, and a subset of negative, patients were selected for laboratory reference tests, clinical examination, and a brain computed tomography (CT) scan (stage 2). For groups 2 and 3, a similar design was adopted, but clinical examination and a brain CT scan (stage 2) were only performed in patients who were TS POC test-positive for cysticercosis. Due to the lack of a gold standard, a Bayesian approach was used to determine test accuracy for taeniosis and cysticercosis. For neurocysticercosis, a composite case definition was used as the reference standard. If successful, this study will help the future developments (commercialization and implementation) of the rapid test and improve patient management and disease prevention.

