### 2.3. Study Objectives and Outcomes

The primary objective of the study was to assess the sensitivity and specificity of the TS POC test for the diagnosis of each of the disease presentations (T, CC, and NCC). Due to the lack of a gold standard, three different reference tests were used for the detection of T and CC, respectively (Table 1). The diagnostic accuracy of the TS POC test for the detection of T was determined against two stool-based reference methods (copro antigen ELISA and copro PCR) and a serological test (immunoblot using the recombinant protein rES33). For CC, the reference methods were the EITB-LLGP, rT24H immunoblot, and the B158/B60 monoclonal antibody-based serum antigen ELISA. For NCC, a composite case definition was used as the gold standard based on Del Brutto’s criteria [8]. An overview of the different reference tests included is given in Table 1, and a description of the tests is presented in Section 2.6.

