### 2.7. Clinical Follow-Up, CT Scans, and Patient Management

A procedure as described for the community-based study in Zambia was followed [11]. For group 1, all patients were seen by a doctor (Figure 2) who performed a neurological examination, while for groups 2 and 3 (Figure 3) only study participants TS POC CC-positive were seen by a study doctor. Appropriate eCRFs were used to record patients’ personal and clinical data according to principles of good clinical practices. After the neurological examination, including past and current medical history, a cerebral CT scan with and without contrast was taken. Contrast was used only if there were no clinical contraindications. If two or more months between the initial TS POC test result and the CT scan elapsed, a new TS POC test was performed using only the strip for CC.

The CT scan results were read independently by the senior project neuroradiologist and an NCC expert. For each CT scan, the number, location, and stage of the lesion were recorded. In the case of a discrepancy, a third independent reviewer adjudicated the CT diagnosis. The final NCC diagnosis was determined according to the 2017 criteria of [8]. These were based on clinical symptoms, neuroimaging, the detection of antibodies and antigens in serum, and epidemiological considerations corresponding to absolute, major, and minor criteria and resulting in the definite and probable diagnosis of NCC. An absolute neuroimaging criterion for NCC was at least one cystic lesion showing the scolex. Major neuroimaging criteria were cystic lesions without scolex, single or multiple rings, or nodular enhancing lesions, multilobulated cystic lesions in the subarachnoid space, and parenchymal brain calcifications. Hydrocephalus or abnormal enhancement of basal leptomeninges were categorized as minor neuroimaging criteria. Four different stages of lesions were defined: vesicular, colloidal vesicular, granular nodular, and nodular calcified. The first three were considered as active NCC lesions and the last was defined as an inactive NCC lesion [8]. 

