### 2.11. Sample Size and Statistical Analysis

The sample size for group 1 was calculated to obtain the desired half-width of 5% around the 95% confidence interval for sensitivity and specificity [22]. Assuming a sensitivity of 93%, a specificity of 99% [11], and a prevalence of NCC of 20%, 500 participants were required. To account for losses, 20% were added to this number. The final sample size for group 1 was set at 600.

Since the prevalence of T in the study population was unknown, the sample size for groups 2 and 3 was calculated for different plausible values, ranging between 3% and 10%. Assuming a sensitivity of 82%, a specificity of 81%, and the desired precision of 10%, 1890 participants were required. To account for 5% contingencies, the final sample size was rounded to 2000 patients.

The sensitivity and specificity of the TS POC test for the detection of T, CC, and NCC were determined relative to the reference tests as shown in Table 1, for each of the three study groups. Weighting was used to correct for the study design (a subset of T-CC that is selected for sampling/clinical examination). The positive and negative predictive values were also determined.

For T and CC, the diagnostic sensitivity and specificity of the TS POC test were estimated using a Bayesian approach as described previously [23]. For the evaluation of the TS POC test performance for NCC, sensitivity and specificity were computed by cross-tabulating POC results with those of the final NCC diagnosis. More details can be found in [11].

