**Figure 3 diagnostics-11-01528-f003:**
[figure not shown]
Flow of the diagnostic accuracy study in Tanzania for patients attending the mental health ward or outpatient department of district hospitals with on-going symptoms of severe progressive chronic headache impeding their daily activities without fever and signs of cerebral infection or other obvious causes; and/or a history of one or more epileptic seizures without obvious causes (group 1). In this two-stage design, all patients were tested using the TS POC test (=index test; stage 1), after which all positive, and a subset of negative, patients were selected for different reference tests, clinical examination, and a brain CT scan (stage 2).

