**Figure 4 diagnostics-11-01528-f004:**
[figure not shown]
Flow of the diagnostic accuracy study in Tanzania for patients attending the outpatient department of district hospitals with symptoms of intestinal worm infections (group 2) and other symptoms (group 3) that were not specific neurological signs and symptoms. In this two-stage design, all patients were tested using the TS POC test (=index test; stage 1), after which all positive, and a subset of negative, patients were selected for different reference tests. Clinical examination and a brain CT scan (stage 2) were only performed on patients positive for CC on the TS POC test.

**Table 1 diagnostics-11-01528-t001:** Reference tests used to assess the sensitivity and specificity of the TS POC test for the detection of taeniosis, cysticercosis, and neurocysticercosis.

Disease Presentation	TS POC Test Strip	Purpose	Reference Standard
Taeniosis	TS POC T	Diagnosis/treatment Monitoring/surveillance Epidemiological research	copro antigen ELISA (stool ag) copro PCR (stool DNA) rES33 immunoblot (serum ab)
Cysticercosis	TS POC CC	Monitoring/surveillance Epidemiological research	EITB-LLGP (serum ab) rT24H immunoblot (serum ab) serum antigen ELISA (serum ag)
Neurocysticercosis	TS POC CC	Diagnosis/treatment and management Epidemiological research	Composite case definition according to Del Brutto et al.’s criteria [8]

TS POC T: *Taenia solium* point-of-care test taeniosis test strip; ELISA: enzyme-linked immunosorbent assay; PCR: Polymerase Chain Reaction; TS POC CC: *Taenia solium* point-of-care test cysticercosis strip; EITB: enzyme-linked immunoelectrotransfer blot; LLGP: lentil lectin-bound glycoproteins.

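### NCC sensitivity, specificity and NPV are claimed for all three groups, but groups 2 and 3 have no verified CC-negative patients, so none can be estimated there

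*Protocol article*

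**What the plan says.** Section 2.3 makes accuracy for taeniosis (T), CC and NCC the primary objective and takes a composite case definition as the NCC reference standard. Section 2.7 builds that definition from imaging, clinical, serological and epidemiological findings.

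Section 2.11 states that sensitivity and specificity for "T, CC, and NCC were determined relative to the reference tests as shown in Table 1, for each of the three study groups". It goes on: "The positive and negative predictive values were also determined", with no limit by disease or group. For NCC the method is that "sensitivity and specificity were computed by cross-tabulating POC results with those of the final NCC diagnosis". The section also mentions weighting to correct for the sampled subset.

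Who receives the NCC reference standard depends on the group. In group 1, all index-positives and a subset of index-negatives go on to reference tests, examination and CT (Abstract; Figure 3 legend). For groups 2 and 3, the Figure 4 legend says: "Clinical examination and a brain CT scan (stage 2) were only performed on patients positive for CC on the TS POC test". The Abstract gives the same restriction, and Section 2.7 adds that in these groups "only study participants TS POC CC-positive were seen by a study doctor". The sampled negatives in groups 2 and 3 receive laboratory reference tests only.

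**The concern.** A sensitivity needs the diseased patients whom the test missed, and a specificity needs the non-diseased patients whom it cleared. Both kinds of patient are index-negative. In groups 2 and 3 no CC-negative patient has the imaging or the examination, so none has a final NCC diagnosis. This is an extreme form of partial verification: the negatives are not under-sampled, they are not verified at all.

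Section 2.2 justifies the three groups on the ground that accuracy probably differs between types of patient. Group-specific NCC accuracy is thus part of the design's rationale, and the group 1 result cannot simply stand in for the other two groups. If the analysis were run as written, groups 2 and 3 would yield artefacts for a primary-objective quantity. If their scanned positives were pooled with group 1, they would add true and false positives but no negatives, which pushes sensitivity up and specificity down.

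**Working it through.** **What each group was sized for.** The formula is n = 1.96² × Se(1 − Se) / d² / prevalence, with inputs from Section 2.11.

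- Group 1 (Se 93%, d = 5%, NCC prevalence 20%): 3.8415 × 0.93 × 0.07 / 0.0025 / 0.20 = 500.2. The article states 500.
- Groups 2 and 3 (Se 82%, d = 10%, T prevalence 3%, the lowest value considered): 3.8415 × 0.82 × 0.18 / 0.01 / 0.03 = 1890.0. The article states 1890.

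Both figures reproduce. Only group 1 was sized on NCC; groups 2 and 3 were sized on T.

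**The NCC table in groups 2 and 3 under the stated verification rule.**

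| | NCC | no NCC |
|---|---|---|
| CC strip positive | TP observed | FP observed |
| CC strip negative | FN not observed | TN not observed |

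Among verified patients FN = 0 and TN = 0 by construction. Hence:

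- sensitivity = TP / (TP + 0) = 100%
- specificity = 0 / (0 + FP) = 0%
- NPV = 0 / 0, undefined
- PPV = TP / (TP + FP), estimable

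The inverse-probability weight for the negative row would be 1/0. If, for example, 10% of the 2000 patients were CC-positive, 1800 would have no chance of verification.

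**How little the data say about sensitivity.** The article gives no NCC prevalence for groups 2 and 3, so I assume N = 2000, prevalence 1%, true sensitivity 93% and true specificity 99%.

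- TP = 2000 × 0.01 × 0.93 = 18.6
- FP = 2000 × 0.99 × 0.01 = 19.8
- unverified negatives = 2000 − 18.6 − 19.8 = 1961.6
- PPV = 18.6 / 38.4 = 48.4%

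Let π be the unknown NCC rate among the unverified negatives. Then sensitivity = 18.6 / (18.6 + 1961.6π) and specificity = 1961.6(1 − π) / (1961.6(1 − π) + 19.8).

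| π | Sensitivity | Specificity | NPV |
|---|---|---|---|
| 0 | 100% | 99.0% | 100% |
| 0.1% | 90.5% | 99.0% | 99.9% |
| 1% | 48.7% | 99.0% | 99.0% |
| 5% | 15.9% | 98.9% | 95.0% |
| 100% | 0.9% | 0% | 0% |

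Every row fits the same observed data. Varying the assumed prevalence (1%, 2%, 5%) and true sensitivity (50%, 70%, 93%) changes the PPV, from 33.6% to 83.0%, but the verified table gives 100% and 0% each time.

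**Effect of pooling, were it done.** Take group 1 at its planning values with 600 patients and its negatives fully restored by weighting: TP 111.6, FN 8.4, FP 4.8, TN 475.2. Adding 18.6 TP and 19.8 FP from groups 2 and 3:

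- sensitivity goes from 93.0% to 130.2 / 138.6 = 93.9%
- specificity goes from 99.0% to 475.2 / 499.8 = 95.1%

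**The case against.** The best counter-argument concerns specificity. Everyone is index-tested, so the number of CC-negatives is known, and the 0% figure appears only if they are dropped. With 200 positives and 1800 negatives, all positives counted as false, and NCC among negatives between 0% and 20%, specificity lies between 1440/1640 = 87.8% and 1800/2000 = 90.0%. That is correct arithmetic, but the 20% ceiling is an outside assumption that the article does not make. Without it, specificity can lie anywhere from 0% to the upper bound. Sensitivity stays unidentified even under modest values of π.

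Other points carry some weight:

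- The sentence on predictive values names no group or disease. It does, however, directly follow the by-group statement without restriction.
- The article does not propose pooling NCC results, so that harm is conditional.
- The objective in Section 2.3 makes no by-group claim, and the sample sizes suggest that NCC accuracy was expected from group 1. At most, the objective needs a matching clarification.

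The article is condensed and refers to the design paper of the companion Zambian study, which is not shown, for details. That does not settle the matter. The article makes an affirmative statement that its own design rules out, and no analysis detail can supply an NCC diagnosis for patients without CT or examination. Declaring CC-negatives free of NCC would fix sensitivity at 100%.

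**Conclusion.** The concern holds. Section 2.11 contradicts the Abstract, Section 2.7 and the Figure 4 legend. In groups 2 and 3, NCC sensitivity, specificity and NPV cannot be estimated from this design, and the stated cross-tabulation gives 100%, 0% and undefined. This follows from the verification rule alone and needs no assumption about prevalence or accuracy. The range of sensitivities from 100% to 15.9%, and the pooled shift in specificity from 99.0% to 95.1%, are illustrations that rest on the assumed values above. The NCC analysis in group 1 is not affected by this point, nor are the T and CC analyses. It must be fixed because NCC accuracy belongs to the primary objective.

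**What to change.** In Section 2.11, restrict NCC sensitivity, specificity and NPV to group 1. For groups 2 and 3, state that only two NCC quantities are reported: the PPV of the CC strip with its 95% confidence interval, and the yield of CT-confirmed NCC per patient tested. State that groups 2 and 3 do not enter any pooled NCC sensitivity or specificity. Add a matching clarification to the objective in Section 2.3, and mark in Table 1 the group to which NCC accuracy applies.

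If the authors still want to comment on specificity or NPV in groups 2 and 3, they should present bounds over a stated range for the NCC rate among CC-negatives, labelled as assumption-based.

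The cost is wording: no further patients and no further data. The price is a narrower claim, with NCC accuracy established only for patients with neurological signs and symptoms.

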## 3. Discussion

This trial was designed to provide a rigorous evaluation of TS POC test accuracy for the detection of T, CC, and NCC. The ambitious four-year project was the result of longstanding North–South collaborations and aimed at including 2600 patients of three district hospitals in Tanzania. If the test is validated with success, it may be proposed for commercialization and implementation at district hospitals and community health centers in endemic areas. 

As several sources of bias can arise in diagnostic accuracy studies [24], several measures were taken to assure the internal validity of our study. As unblinded studies may have a higher sensitivity and overall accuracy of results when the person interpreting the reference standard is aware of the index test result [25], diagnostic review bias in the present study was avoided by blinding all laboratory technicians to the TS POC test result. Moreover, as the interpretation of several reference test results for T and CC have inherent test integrity (such as ELISA results, which are read by a spectrophotometer), diagnostic review bias seemed very unlikely for the evaluation of T and CC. On the other hand, clinical examination, and interpretation of CT scans, which were both used for the composite case definition for NCC, are more subjective. Therefore, a structured questionnaire was used to record the results of the neurological examinations to reduce subjectivity in the examinations as much as possible. Moreover, all CT scans were read in detail by two independent readers, and in the case of a disagreement, additionally by a third independent reader, who were all blinded to the TS POC result. 

Stool and serum samples for the reference tests were requested immediately after performing the TS POC test to reduce loss-to-follow-up and to avoid disease progression bias. Although we aimed to perform the CT scans with minimal delay, the CT scans could not always be performed within a reasonable time frame after the index test due to several logistical reasons (such as an inoperative CT scanner and travel planning of the neurology team to be present when CT scans were taken). Since delayed verification may result in biased accuracy estimates [25], an additional TS POC test was performed on patients for whom more than two months had passed between the initial TS POC test and CT scanning. These results were used to assess the extent of disease progression bias.

As disease severity and participant demographics can influence test accuracy, the TS POC test evaluation in the SOLID project included different groups of patients attending the district hospitals for which the test may be used in practice. Moreover, to increase generalizability, three different district hospitals were chosen in the design. To obtain a representative sample of the different studied populations, patients attending the outpatient department (and the mental health ward for patients with specific neurological signs and symptoms) were recruited consecutively for groups 1 and 2, and selecting every tenth patient in group 3. Although several efforts were made to increase the external validity of the study, results may not be generalizable to patients attending local healthcare facilities or other more specialized hospitals, where differences in disease spectrum or other underlying (demographic) factors might be present.

If successful, the tool will be the first POC test contributing to NCC diagnosis which could be made available at the district hospital level. Combined with increased knowledge, training, and capacity building, this project aided staff at the district hospital level to identify, correctly and early, suspected NCC cases. Furthermore, thanks to the training, staff will be able to make the connections between NCC on the one side and epileptic seizures/epilepsy, severe progressive chronic headache, and other neurological signs/symptoms on the other side. Finally, we do hope that patients will be referred to neuroimaging facilities or more specialized hospitals when necessary. This will lead to improved patient management practices, contributing to a positive effect on the patients’ health outcome, and raising awareness of *T. solium*-associated neurological diseases, e.g., epileptic seizures/epilepsy, which bear an enormous burden of the disease, especially in LMIC [26]. NCC is one of the main causes of epileptic seizures/epilepsy in *T. solium*-endemic areas [27] and it is a curable disease. A POC test clearly has the potential to contribute to changing the narrative around epilepsy being a chronic disease with often high mortality in LMIC [26] to a curable disease in *T. solium*-endemic areas. Additionally, a correct diagnosis and knowledge of NCC will potentially stimulate the people’s perception of epilepsy as being a biological disease (e.g., NCC as its cause) rather than a consequence of witchcraft, which is a common belief in the study area [28]. Creating awareness and educating professionals in disease recognition will further lead to an increased number of detected cases. If the TS POC test proves to have acceptable sensitivity and specificity to detect NCC cases, further studies are required to evaluate the TS POC test’s ability to guide clinical decision-making [29].

The TS POC test will be the first portable, easy-to-apply diagnostic test for T available at the district hospital level. This will lead to the early detection and treatment of tapeworm carriers. The latter is crucial to reduce/stop disease transmission as tapeworm carriers are responsible for environmental contamination with infective eggs. These carriers represent a risk not only for themselves but also for their close contacts. Early detection and treatment will ensure a rapid halt to this environmental contamination, reducing the risk of new NCC cases and the infection of pigs, and thus, of perpetuating the life cycle. The training will guide the staff in the treatment and follow-up of tapeworm carriers at the household and community level.

Adequate monitoring and surveillance systems, which are necessary to support the sustainable control of *T. solium*, are currently not implemented in sub-Saharan Africa, largely due to the lack of well-performing tests that are deployable in low-resource settings. Therefore, as well as its diagnostic use, the TS POC may also be used for monitoring and surveillance purposes, as it is affordable, relatively rapid, equipment-free, and user-friendly [14]. For this aim, the TS POC test was also validated for use at the community level in Zambia, which mainly included asymptomatic people [11].

In Tanzania, in contrast to Zambia, the study was conducted primarily by trained hospital staff, and recruitment and testing occurred daily until the target sample size was obtained. To assure the smooth conduct of the study and the correct following of study standard operating procedures, the intensive training of staff involved in the study was essential. In the SOLID project, new digital tools for data collection with barcoding systems were introduced, which might have posed a challenge to members of staff more used to traditional data recording methods. However, the digitalization of data collection was chosen for the SOLID project to be able to monitor study progress by assessing the number of entries uploaded, to assist staff when issues might appear during regular data checks, cleaning, and validation sessions performed by project members, on top of advancing technological knowhow in resource-limited areas. To assure high-quality data collection, correct patient follow-up, and adequate sample collection, processing and storage, the district hospital staff was monitored by project members’ fortnightly visits.

